### Sample size

General practices with a screening uptake rate of less than 50% will be purposively recruited. Assuming an average GP list size of 2,750 (information derived from the MidReC general practice database), with 11.8% of the population aged between 60 and 74 years old [26], and a bowel cancer screening participation rate of 45%, there will be 146 eligible individuals per practice (Figure 1). Thirty practices will provide 4,380 people for randomisation to the intervention or control arms of the trial. Assuming a screening uptake rate of 3.2% in the control arm (Midlands and North West Screening Hub recorded rate of delayed FOBt return amongst previous non-responders), a comparison of proportions test shows that a sample size of 934 in both the intervention and control groups is required in order to demonstrate a doubling of the uptake rate (from 3.2% to 6.4% or more) with 90% power at the 5% significance level. The larger number of patients (n = 2,190 in each group) has been chosen in order to enable sub-group analyses to be undertaken, and to account for any effects of nesting of patients within general practices should interim analyses demonstrate that such nesting is occurring.

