### Study population

The study population will be adults aged between 60 and 74, on the patient list of a general practice where the bowel screening uptake rate is < 50%, who were invited to participate in the most recent round of bowel screening but who have not returned their FOBt within the 13 week 'screening episode' recorded by the Midlands and North West Bowel Cancer Screening Hub.

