### Participant selection

Participant selection will be undertaken in two stages. First, the Midlands and North West Bowel Cancer Screening Hub will identify general practices in the West Midlands where the uptake of bowel cancer screening is lower than 50%. The contact details of these practices will be obtained via the MidReC (Midlands Research Practices Consortium) database, and all eligible practices will be contacted by the research team at the University of Birmingham and invited to participate, with general practice recruitment continuing until a total of up to 30 practices have been recruited. Once practices have been recruited, the Hub will identify all eligible screening non-responders aged 60 to 74 at each participating practice. Non-responders will be defined as those who have not responded to either the initial invitation to screening, or the 4-week reminder, within a period of 13 weeks after being invited.

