#### Feasibility

If the GP endorsed reminder is successful, we expect around 140 FOBt kits to be returned by patients randomised to the intervention arm of the trial. We aim to invite all patients in the trial intervention arm who returned a FOBt kit for interview, and conservatively estimate a response rate of 25% based on recruitment levels achieved in previous qualitative studies associated with bowel cancer screening uptake ([name] *et al. *personal communication). This would equate to approximately 35 individuals willing to participate in the qualitative phase.

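### The yield of 146 eligible people per practice uses the 45% who take part in screening; the trial enrols the 55% who do not, so 4,380 is not what thirty practices would give on the stated inputs

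*Protocol article*

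**What the plan says.** The Sample size section builds the expected yield from three inputs: "Assuming an average GP list size of 2,750", "with 11.8% of the population aged between 60 and 74 years old", and "a bowel cancer screening participation rate of 45%, there will be 146 eligible individuals per practice". It then concludes: "Thirty practices will provide 4,380 people for randomisation to the intervention or control arms of the trial". The same total, or its half of 2,190 per arm, is repeated in the Abstract, in the opening of Methods/design and under Randomisation.

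Eligibility is defined by not taking part. Under Study population the trial is for people "who were invited to participate in the most recent round of bowel screening but who have not returned their FOBt". Under Participant selection, "the Hub will identify all eligible screening non-responders aged 60 to 74 at each participating practice". The practices themselves are chosen for low uptake: "General practices with a screening uptake rate of less than 50% will be purposively recruited".

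In the qualitative study, the Feasibility section states that, if the reminder works, "we expect around 140 FOBt kits to be returned by patients randomised to the intervention arm of the trial". A 25% response to the interview invitation then gives about 35 interviewees.

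**The concern.** A participation rate of 45% leaves 55% who did not participate, and only they can enter the trial. The figure of 146 appears to have been obtained from the wrong one of these two shares.

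The number of eligible people per practice is a core planning quantity in a feasibility study, and the Discussion says the findings will be used to design and power a definitive trial. If the observed yield is later judged against a benchmark that counted the wrong group, recruitment will be misread and the slip may carry over. There is also an immediate ambiguity. The Hub is to identify every eligible non-responder at each practice, while the Randomisation section fixes the total at 4,380. On the plan's own inputs, thirty practices and 4,380 people do not agree, and the article does not say which governs.

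**Working it through.** **Inputs, all from the Sample size section unless noted.** List size 2,750; share aged 60 to 74, 11.8%; screening participation 45%; thirty practices; equal allocation; uptake 3.2% in the control arm and 6.4% under the intervention; interview response 25% (Feasibility section).

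**The plan's own figures.**
- People aged 60 to 74 per practice: 2,750 × 0.118 = 324.5
- Times 0.45: 324.5 × 0.45 = 146.0, the stated 146
- Thirty practices: 30 × 146 = 4,380; per arm 4,380 / 2 = 2,190
- Returned kits: 2,190 × 0.064 = 140.2, the stated 140
- Interviewees: 140 × 0.25 = 35, as stated

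Every figure reproduces, and 146 does so only with the participation rate.

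**The same chain with the share who did not take part.**
- Per practice: 324.5 × 0.55 = 178.5 (178.5 / 146.0 = 1.22, so 22% more)
- Thirty practices: 30 × 178.475 = 5,354; per arm 2,677
- Difference from plan: 5,354 − 4,380 = 974 in total, 487 per arm
- Practices needed for 4,380: 4,380 / 178.475 = 24.5, so 25
- Returned kits if all were randomised: 2,677 × 0.064 = 171; interviewees 171 × 0.25 = 43

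**Could 146 be right for some other uptake the plan allows?** Practices must have uptake below 50%. At exactly 50% the stated inputs give 324.5 × 0.50 = 162 non-responders, and any lower uptake gives more. So 146 cannot arise from these inputs within the plan's own entry rule.

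**What does not depend on 146.** The required size for 3.2% against 6.4%, two-sided 5%, 90% power, comes to 936 per arm with pooled variance and 933 unpooled, against the stated 934. Ignoring clustering, power is 90% at 934 per arm and 99.9% at 2,190 per arm; 2,190 / 934 = 2.3.

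**The case against.** Four points can be made for the plan.

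1. *The 45% might be a slip for the share who do not take part, or might mean participation in the trial.* Neither reading works. The first implies 55% uptake, which breaks the below-50% entry rule. The second conflicts with the wording, which names screening participation, and with the plan to randomise without consent.

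2. *Exclusions or the eligibility window might bring 178 down to 146.* That would take a loss of 1 − 146 / 178.5 = 18%. The section states no such loss, and 146 equals the 45% product exactly. Figure 1, cited at this step, is not available here, but it cannot change the product of the stated inputs.

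3. *The total is a choice, not a derivation.* This stands in part. The article speaks of up to thirty practices and approximately 4,380 people, and says the larger arm size was chosen to allow for subgroup analyses and nesting. So 4,380 can be kept as a target. It cannot be kept as what thirty practices would provide on these inputs.

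4. *The error is harmless.* This stands for power. The slip understates the yield, and 934 per arm does not rest on it.

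A reader might infer that every figure in the section is wrong. The document does not support that. The 934 and its 90% power stand, thirty practices is an input, and 140 kits and 35 interviewees are correct for 2,190 per arm. They change only if the arm size changes.

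**Conclusion.** The point holds as a moderate error in a stated planning figure. On the protocol's own inputs, 146 per practice should be about 178, and thirty practices would give about 5,350 people rather than 4,380. The primary comparison, the randomisation and the required sample size are not affected.

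This rests on the three stated inputs and on treating everyone aged 60 to 74 who did not take part as a recorded non-responder. The 178 is therefore a figure before losses and should not be read as the final yield. Nor should one infer that 25 practices will suffice. The exclusion criteria and the restriction to people recorded as non-responders one to seven months earlier both pull the number down, and the article gives no rate for either. If together they remove more than 1 − 4,380 / 5,354 = 18%, thirty practices would fall short of 4,380.

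As an illustration only, assume that invitations are spread evenly over the two-year cycle and that each practice's list is drawn once. The window then keeps 6/24 of non-responders, and thirty practices give 5,354 × 0.25 = about 1,340. With no loss the figure is 5,354, so the range is wide. That is a separate matter. It depends on invitation timing that the article does not state, and it neither rescues 146 nor shows that this slip leaves the trial underpowered.

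**What to change.** Redo the yield derivation in the Sample size section with 0.55 in place of 0.45, and state explicit allowances for the exclusion criteria and the one-to-seven-month window. Then choose one of two courses and say which governs:

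- **Keep the target.** Present 4,380 (2,190 per arm) as a chosen size and state that practice recruitment stops when it is reached. The 140 kits and 35 interviewees then stand. The cost is rewording only, with no change in the number randomised.
- **Keep thirty practices and enrol all who are eligible.** Restate 4,380, 2,190, 140 and 35 from the corrected yield wherever they appear. This changes the number of people randomised and kits sent, and the article should say so. Before allowances it means up to 974 more people, 487 of them receiving a letter and kit. The interview plan hardly changes, since recruitment there stops at 30 to 40 interviews or at saturation.

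The 934 per arm needs no change under either course. The article reports that recruitment had not begun at submission, so on that account the correction can be made before anyone is randomised.

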**Figure 1 F1:**
[figure not shown]
**Study schematic**.

### Qualitative study

Previous research exploring the patient factors associated with bowel cancer screening participation has provided limited information about significant sociodemographic and psychosocial factors, but the relative importance of these is unknown, and research has often yielded conflicting information [27]. Multi-factorial approaches, combining behavioural and educational strategies with healthcare interventions such as GP endorsed screening reminders are likely to be an important means of addressing the low uptake of CRC screening in the long term. Qualitative methodologies are a highly appropriate means of eliciting information about beliefs, attitudes and knowledge, and the ways that individuals justify their decision-making, particularly where the factors of concern may be unclear. Undertaking an embedded qualitative study will allow us to begin to understand the relative influence on individual decision-making of the three components of this intervention - receiving a reminder, receiving a duplicate FOBt kit, and endorsement of screening by an individual's GP.

#### Population

Approximately 30 to 40 individuals in the intervention arm of the study, who return their FOBt kit after receiving a reminder from their GP, will be recruited to participate in a semi-structured interview to investigate their reasons for returning the kit.

#### Recruitment

The Hub will send a letter inviting participation in a semi-structured interview to all individuals who have returned a FOBt kit following the intervention. A reply slip, on which patients can indicate their willingness to be interviewed, will be enclosed with the invitation letter, which will be returned to the University of Birmingham so that an interview can be arranged. All non-responders to an invitation to participate in an interview will receive one reminder from the screening Hub. Recruitment to the qualitative study will continue until data saturation has been reached, or until 30 to 40 interviews have been undertaken.

#### Feasibility

If the GP endorsed reminder is successful, we expect around 140 FOBt kits to be returned by patients randomised to the intervention arm of the trial. We aim to invite all patients in the trial intervention arm who returned a FOBt kit for interview, and conservatively estimate a response rate of 25% based on recruitment levels achieved in previous qualitative studies associated with bowel cancer screening uptake ([name] *et al. *personal communication). This would equate to approximately 35 individuals willing to participate in the qualitative phase.

#### Data collection

Interviews will take place either in a location of the participant's choice, or by telephone, and will be conducted by an experienced qualitative researcher. The topic guide will focus on attitudes and beliefs about bowel cancer screening, reasons for previous participation and/or non-participation in screening, and reasons for participation following the trial intervention. All interviews will be digitally audio-recorded and transcribed, and each will last approximately 60 minutes.

### Analysis

Trial data will be analysed on an intention to treat basis. The primary outcome measure (screening uptake in the intervention and control arms of the trial) will be analysed using a non-linear mixed logit model for dichotomous outcomes, accounting for practices as random effects. Secondary analyses will include comparison of screening uptake rates by sub-group on the basis of patient characteristics (age, gender, deprivation); whether or not the GP letter template was modified by a participating practice; previous bowel cancer screening behaviour, and according to the time period between an individual's first screening episode and the intervention. A multivariable prognostic model will be developed, incorporating interaction terms between factors. Decision tree analysis will also be undertaken, and the findings from these complementary analytical approaches will be cross-validated in order to identify factors predictive of delayed participation in the NHSBCSP [28]. Evaluating the potential influence of previous bowel screening behaviour on screening uptake rates within the feasibility work will inform the design of any future definitive trial with regard to establishing the need to stratify trial participants according to past screening behaviour prior to randomisation.

The characteristics of participating and non-participating general practices (i.e. those who were invited but who declined to participate) will be compared, using information derived from the MidReC general practice database in order to ascertain practice compliance rates and to investigate potential selection bias and confounders at the practice level. Comparisons will be made with regard to practice list size and other GP/practice-related factors (e.g. whether a practice is single-handed or has multiple partners; the socioeconomic deprivation profile of the practice catchment area, and the proportion of ethnic minority patients within the geographical area covered by the practice). These analyses will inform the design and methodology of any future definitive trial of the intervention.

Analysis within the qualitative study will be carried out by reading the interview transcripts and identifying emerging themes and categories. Each transcript will be independently analysed by two experienced qualitative researchers using thematic analysis. Themes arising from each interview will be compared in order to detect similarities and differences, and a constant comparative approach will be used, so that important themes arising from earlier interviews can be incorporated into a flexible topic guide for exploration in subsequent interviews.

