### Outcome measures

The primary outcome measure will be the difference in the uptake rate of FOBt screening for bowel cancer (i.e. the proportion of individuals who return a FOBt kit to the screening Hub) between the intervention and control group after 13 weeks.

Secondary outcome measures will include sub-group analysis of screening uptake rates following the intervention, according to age, gender and deprivation quartile, and the development and validation of methods and proformas for collecting information on GP, NHSBCSP and patient costs associated with the intervention. Such costs are anticipated to include the cost to the Hub of sending GP reminders to screening non-responders; costs associated with staff workload in sending reminders; time costs for participants, and costs to primary care if the intervention results in an increased number of patients contacting their GP to discuss bowel cancer screening.

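### The primary outcome is defined and powered as a difference in uptake proportions, but the stated primary analysis is a practice random-effects logit that yields an odds ratio and names no baseline covariates

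*Protocol article*

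**What the plan says.** Under Outcome measures, the protocol article states: "The primary outcome measure will be the difference in the uptake rate of FOBt screening for bowel cancer" (with uptake defined as the proportion of people returning a kit), "between the intervention and control group after 13 weeks". The Abstract defines the outcome in the same way.

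The Sample size section works on that scale. It begins "Assuming a screening uptake rate of 3.2% in the control arm", takes a doubling to 6.4% as the target, and uses a comparison of two proportions "with 90% power at the 5% significance level" to reach 934 per arm. The planned size is 2,190 per arm.

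The Analysis section then says that the primary outcome "will be analysed using a non-linear mixed logit model for dichotomous outcomes, accounting for practices as random effects". It mentions no risk difference, no step from the model back to proportions, and no patient-level covariate. Age, gender, deprivation and previous screening behaviour appear there only in secondary subgroup comparisons, alongside a separate prognostic model. On past behaviour the text is tentative: "Evaluating the potential influence of previous bowel screening behaviour on screening uptake rates within the feasibility work will inform the design" of any later definitive trial.

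**The concern.** The plan names a quantity in one section and a model in another, and the model's treatment coefficient is not that quantity. A random-intercept logit estimates a log odds ratio conditional on practice. An odds ratio fixes an absolute difference only once a baseline risk is supplied, and the 3.2% baseline is itself an assumption.

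The scale matters for the trial's declared use. The Discussion says that the definitive trial will be designed and powered from these results and would go on to assess cost-effectiveness by sub-group. Both tasks start from uptake by arm and the absolute gain, with its uncertainty. If the primary result is printed as an odds ratio, readers have to reconstruct the figure that the protocol called primary, and its confidence interval may be missing.

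The second, smaller matter is that randomisation is blocked by practice only. Baseline variables already needed for the secondary analyses could therefore sharpen the primary estimate, but the primary model as described does not use them.

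**Working it through.** **Inputs from the protocol article.** Control uptake 3.2%, intervention uptake 6.4%, power 90%, alpha 5%, 934 per arm required, 2,190 per arm planned (Sample size); 1:1 allocation blocked within practice (Randomisation).

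**Inputs assumed, because the article gives none.** Between-practice ICC on the latent logit scale, 0.01 to 0.20. SD of a normally distributed prognostic index on the logit scale, 0.25 to 1.5. Baselines of 1% and 8%, for illustration only.

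**1. Reproduce the plan's figure.** Sum of variances: v = 0.032 × 0.968 + 0.064 × 0.936 = 0.09088. Unpooled, two-sided: n = v × (1.960 + 1.282)² / 0.032² = 933. With the pooled variance under the null, n = 936. The stated 934 is reproduced (power at 934 is 89.9%), which confirms that the trial was sized on proportions.

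**2. The same effect on the model's scale.** OR = (0.064/0.936) / (0.032/0.968) = 2.068.

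**3. What that odds ratio implies at other baselines.** p₁ = OR × odds₀ / (1 + OR × odds₀).

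| Baseline | Difference at OR 2.068 |
|---|---|
| 1% | +1.0 point |
| 3.2% | +3.2 points |
| 8% | +7.2 points |

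**4. Precision on the stated scale.** SE = √(0.09088 / 2190) = 0.0064, so the 95% half-width is 1.96 × 0.0064 = 0.0126, about 1.3 points before any clustering allowance. Power at 2,190 per arm is 99.9% on the same basis.

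**5. Does conditioning on practice matter?** Marginal risks were held at 3.2% and 6.4% and a normal random intercept integrated out.

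| Assumed latent ICC | Conditional OR |
|---|---|
| 0 | 2.068 |
| 0.01 | 2.071 |
| 0.02 | 2.073 |
| 0.05 | 2.081 |
| 0.10 | 2.096 |
| 0.20 | 2.138 |

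The gap is negligible across 0.01 to 0.10.

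**6. What would baseline covariates buy?** Let p₀ and p₁ be a person's risk under control and intervention, with averages held at 3.2% and 6.4%. The variance (per person per arm) of an efficient adjusted difference is E[p₀(1−p₀)] + E[p₁(1−p₁)] + ½Var(p₁−p₀), compared with v = 0.09088 unadjusted.

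| Assumed index SD | Variance saved | Power at 934 per arm | Covariate-conditional OR |
|---|---|---|---|
| 0.25 | 0.3% | 90.0% | 2.073 |
| 0.5 | 1.2% | 90.3% | 2.086 |
| 1.0 | 5.5% | 91.5% | 2.157 |
| 1.5 | 12.8% | 93.4% | 2.304 |

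The gain is small unless prediction is very strong. The last column shows that the conditional odds ratio moves with the covariates chosen, while the standardised difference stays at 3.2 points by construction.

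**The case against.** The best case for the plan is that nothing in it is contradictory. The outcome is fixed as a difference and the Analysis section names a model; it never says that an odds ratio will be the reported result. A mixed logit can produce a risk difference, and a condensed article may leave that step, and the covariate list, to a fuller document. The Hub also logs kits returned in each arm, so the crude difference can be computed from the counts. With power near 99.9% before clustering, a few per cent of variance has little bearing on the test. Chance imbalance is minor too: for an assumed factor with 30% prevalence, the SD of the between-arm imbalance is √(2 × 0.3 × 0.7 / 2190), about 1.4 points. At an assumed odds ratio of 3 that shifts the difference by roughly 0.1 point, against an SE of 0.64.

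Much of this stands. The absence of a covariate list is not an error, and an unadjusted comparison with practice as a random effect is valid and suits the blocking. What remains is that the article does state both the primary measure and the primary model, and the second does not by itself deliver the first with a confidence interval. A crude difference would also leave the practice structure, which the stated model was chosen to handle, out of the interval.

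A reader might go further and infer that strong predictors held by the Hub have been left out. The article does not support that. It gives no strength for any covariate and treats the influence of past behaviour as a question for this study. It does not state where deprivation data come from. It neither lists nor excludes patient covariates for the primary model.

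**Conclusion.** The point holds as a mismatch of reporting scale, with a small amount of unused precision beside it. The outcome and sample size are on the difference scale (3.2 points, about ±1.3 at 2,190 per arm before clustering); the named analysis is on the odds-ratio scale (2.07).

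A reader might infer that the test is invalid or that conditioning on practice distorts the effect. Neither follows: the test is sound, and the conditional odds ratio is 2.071 to 2.096 against 2.068 for an assumed ICC of 0.01 to 0.10. The saving from covariates is about 0.3% to 5.5% of variance for an assumed index SD of 0.25 to 1.0, and this range rests wholly on that assumption. The required sample size does not change. The amendment is worth making because it serves the stated outcome and the design of the definitive trial at almost no cost.

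**What to change.** Amend the Analysis section as follows:

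- Keep the mixed logit with practice random effects.
- Add age, gender, deprivation and previous screening behaviour as fixed covariates, measured before randomisation. Include only those available for everyone randomised, and settle the list before outcome data are seen.
- Predict each randomised person's uptake probability under both arms, average over all randomised people, and report the difference with its 95% CI as the primary result. State how practice effects enter the predictions and how the interval is computed.
- Report the odds ratio as supporting, with uptake in each arm.

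The cost is a few sentences and a few lines of code. The secondary analyses already need these variables, although the source of deprivation data should be confirmed. Sample size, randomisation and outcome collection are untouched, and the Trial Status section says that recruitment had not begun when the article was submitted.
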